## Abstract

**Background:**

The p.Arg14del (c.40_42delAGA) phospholamban (PLN) pathogenic variant is a founder mutation that causes dilated cardiomyopathy (DCM) and arrhythmogenic cardiomyopathy (ACM). Carriers are at increased risk of malignant ventricular arrhythmias and heart failure, which has been ascribed to cardiac fibrosis. Importantly, cardiac fibrosis appears to be an early feature of the disease, occurring in many presymptomatic carriers before the onset of overt disease. As with most monogenic cardiomyopathies, no evidence-based treatment is available for presymptomatic carriers.

**Aims:**

The PHOspholamban RElated CArdiomyopathy intervention STudy (iPHORECAST) is designed to demonstrate that pre-emptive treatment of presymptomatic PLN p.Arg14del carriers using eplerenone, a mineralocorticoid receptor antagonist with established antifibrotic effects, can reduce disease progression and postpone the onset of overt disease.

**Methods:**

iPHORECAST has a multicentre, prospective, randomised, open-label, blinded endpoint (PROBE) design. Presymptomatic PLN p.Arg14del carriers are randomised to receive either 50 mg eplerenone once daily or no treatment. The primary endpoint of the study is a multiparametric assessment of disease progression including cardiac magnetic resonance parameters (left and right ventricular volumes, systolic function and fibrosis), electrocardiographic parameters (QRS voltage, ventricular ectopy), signs and/or symptoms related to DCM and ACM, and cardiovascular death. The follow-up duration is set at 3 years.

**Baseline results:**

A total of 84 presymptomatic PLN p.Arg14del carriers (*n* = 42 per group) were included. By design, at baseline, all participants were in New York Heart Association (NHYA) class I and had a left ventricular ejection fraction > 45% and < 2500 ventricular premature contractions during 24-hour Holter monitoring. There were no statistically significant differences between the two groups in any of the baseline characteristics. The study is currently well underway, with the last participants expected to finish in 2021.

**Conclusion:**

iPHORECAST is a multicentre, prospective randomised controlled trial designed to address whether pre-emptive treatment of PLN p.Arg14del carriers with eplerenone can prevent or delay the onset of cardiomyopathy. iPHORECAST has been registered in the clinicaltrials.gov-register (number: NCT01857856).

## Introduction

In the Netherlands, approximately 15% of idiopathic dilated cardiomyopathy (DCM) patients and approximately 12% of arrhythmogenic right ventricular cardiomyopathy (ARVC) patients carry a single pathogenic variant, p.Arg14del (c.40_42delAGA), in the *PLN* gene that encodes the phospholamban protein, a regulator of cardiomyocyte calcium cycling (Fig. 1; [1]). The estimated prevalence of this founder mutation is approximately 1:500–1000 in large parts of the Netherlands. Moreover, it has been identified in several other European countries (Germany, Greece, Belgium, Norway, the UK and Spain), and in China, Canada and the United States of America, attesting to its global significance [2].

**Fig. 1 Fig1:**
[figure not shown]
Function of phospholamban. Phospholamban (PLN; *blue arrow*) is a reversibly phosphorylated transmembrane protein that binds to and regulates the activity of the sarcoplasmic reticulum Ca^2+^ ATPase (SERCA2a) pump. *From*: MacLennan et al. Nat Rev Mol Cell Biol. 2003 [27]. Printed with permission from Springer Nature

The clinical phenotype of PLN p.Arg14del carriers is characterised by malignant ventricular arrhythmias, sudden cardiac arrest and progressive heart failure [1, 3–5]. An experimental murine overexpression model of this PLN pathogenic variant found the cardiomyopathy to be characterised by progressive cardiomyocyte loss and severe cardiac fibrosis, and a similar phenotype was observed in a recently developed knock-in model that also recapitulated the clinical findings [6, 7]. Indeed, in our patients, we observed left ventricular myocardial fibrosis even in the presence of preserved (> 45%) left ventricular ejection fraction (LVEF), which suggests that tissue remodelling occurs early on in PLN p.Arg14del carriers, occurring even before onset of overt disease [1, 8, 9]. An earlier study by our group showed that an LVEF below 45% (rather than 35%, as in other types of cardiomyopathy) is an independent risk factor for ventricular arrhythmia in PLN p.Arg14del carriers [3]. We recently refined this observation, showing that left ventricular late gadolinium enhancement (LV-LGE) is an even stronger risk factor than LVEF. In fact, even when LVEF is preserved, LV-LGE appeared to be associated with a higher risk of ventricular arrhythmia in PLN p.Arg14del carriers [9].

Analogous to other inherited cardiomyopathies, the natural course of PLN p.Arg14del cardiomyopathy is age-related; after a presymptomatic phase of variable length, many PLN p.Arg14del carriers progress to overt cardiomyopathy. These patients are treated according to general clinical guidelines for these conditions.

Family cascade screening can, however, identify presymptomatic family members carrying the PLN p.Arg14del pathogenic variant, thereby providing a unique window of opportunity to initiate pre-emptive treatment in carriers before symptoms occur, potentially preventing sudden cardiac death or disease development and progression. However, no evidence-based treatment is currently available for presymptomatic carriers even though early treatment before the onset of any symptoms is potentially of major prognostic importance.

We reasoned that eplerenone, a selective mineralocorticoid receptor antagonist (MRA) with potent antifibrotic properties [10–16], might be effective as an early treatment for PLN p.Arg14del carriers. We are conducting the iPHORECAST trial to investigate whether treatment with eplerenone in presymptomatic PLN p.Arg14del carriers prevents or delays disease onset and symptoms.

## Study design

### Objectives

The objective of the iPHORECAST trial is to show that eplerenone treatment can prevent or reduce progression of disease in presymptomatic PLN p.Arg14del carriers.

### Study population

Specific inclusion and exclusion criteria are listed in Tab. 1. Previously, all known PLN p.Arg14del carriers in the Netherlands, including all presymptomatic carriers, were registered in the PHORECAST registry (PHOspholamban RElated CArdiomyopathy Study; http://www.phorecast.nl). Recently, all carriers have been incorporated in the national arrhythmogenic cardiomyopathy (ACM) registry (www.acmregistry.nl) [17]. We used the PHORECAST registry to recruit eligible presymptomatic subjects. Study participants are between 18 and 65 years of age, have a New York Heart Association (NYHA) functional class of 1 and an LVEF greater than 45% (as measured by cardiac magnetic resonance [CMR]). For ARVC and DCM criteria, we used the revised task force and Mestroni criteria respectively [18, 19]. Carriers taking other cardiovascular medication, including diuretics, angiotensin-converting enzyme (ACE) inhibitors, angiotensin receptor blockers, mineralocorticoid receptor antagonists, beta-blockers and anti-arrhythmic medication, were excluded.

**Table 1 Tab1:** Key inclusion and exclusion criteria

*Key inclusion criteria*
PLN p.Arg14del carriers
Age ≥ 18 and ≤ 65 years
New York Heart Association functional class ≤ 1
LV ejection fraction ≥ 45 (measured with MRI)
*Key exclusion criteria*
Palpitations necessitating treatment (at the discretion of the attending physician)
A diagnosis of DCM (according to the Mestroni criteria [19]). Note: regional LV wall motion abnormalities are acceptable
A diagnosis of ARVC (according to the task force criteria [18])
Global or regional RV dysfunction and/or structural alterations (according to task force criterion 1 [18])
Ventricular premature complexes > 2500 during 24-hour Holter monitoring
Non-sustained ventricular tachycardia during Holter monitoring or exercise testing
History of sustained ventricular tachycardia or ventricular fibrillation
Hypertension requiring the use of antihypertensive drugs, or when this is anticipated within the coming 3 years
Evidence of ischaemic heart disease
Treatment with cardioactive medication
Hyperkalaemia (serum potassium > 5.0 mmol/l)
Severe renal dysfunction (eGFR < 30 ml/min/1.73 m^2^)
Severe hepatic impairment (Child-Pugh class C)
Women who are currently pregnant or report a recent pregnancy (last 60 days) or plan on becoming pregnant
Concomitant use of CYP3A4 inhibitors
Concomitant use of NSAIDs
Concomitant use of potassium-sparing agents
Known intolerance or contraindication for aldosterone antagonists
Participation in another drug trial in which the last dose of drug was within the past 30 days
Contra-indications for CMR (claustrophobia, metal devices)
Subjects unable or unwilling to provide written informed consent

Note: presence of late gadolinium enhancement on CMR is not an exclusion criterion

*PLN* phospholamban*, DCM* dilated cardiomyopathy,* LV* left ventricular, *ARVC* arrhythmogenic right ventricular cardiomyopathy,* RV* right ventricular,* eGFR* estimated glomerular filtration rate,* NSAIDs* non-steroidal anti-inflammatory drug*s, CMR* cardiac magnetic resonance

### Design

This outpatient study is a multicentre, prospective, randomised trial with blinded assessment of endpoints design (PROBE) [20]. The participating centres are the University Medical Center Groningen (which is the coordinating centre and CMR core lab); Amsterdam University Medical Center; Antonius Hospital Sneek and University Medical Center Utrecht. Carriers were randomly assigned to one of the two study arms, either eplerenone or control (no treatment), in a 1:1 ratio. The follow-up period is 3 years (see the section *Study endpoints*).

### Ethical considerations

This study is conducted in accordance with the principles stated in the revised Declaration of Helsinki (Seoul 2008) and in accordance with the Medical Research Involving Human Subjects Act. The medical ethics committee of the University Medical Center Groningen, the Netherlands, approved this study (METc 2013-272; ABR NL43771.042.13; EudraCT 2013-001067-23). The study protocol was also submitted to and approved by the medical ethics committee of each participating hospital. Written informed consent was obtained from every subject before entry into the study. An independent data and safety monitoring board (DSMB) safeguards the interests of i‑PHORECAST trial participants, assesses the safety of the interventions during the trial and monitors the overall conduct of the clinical trial. The study has been registered and kept up-to-date in the clinicaltrials.gov-register (number: NCT01857856).

### Treatment

In the treatment arm, eplerenone was initiated on the day of randomisation at 50 mg orally once daily. The dose of 50 mg once daily is the recommended dose in patients with heart failure. Carriers are maintained at this target dose, or the maximum tolerated dose, until the end of the study. Serum potassium and estimated glomerular filtration rate (eGRF) are monitored at the start of the study, 1–2 week(s) after study start and yearly, and these measures are documented together with the other investigations and vital parameters. The dose is reduced if needed, i.e. in case of hyperkalaemia (serum potassium > 5.5 mmol/l). Carriers undergo yearly follow-up in the cardiology outpatient clinic at each participating centre following routine clinical care. Physical examination, blood sampling (when treated with eplerenone), electrocardiogram, Holter monitoring and ergometry are performed every 12 months. CMR imaging and SA-ECG are performed at the start and end (36 months) of the study (Tab. 2).

**Table 2 Tab2:** Overview of study procedures

	Visit 1 start	Visit 2 1 week	Visit 3 1 year	Visit 4 2 years	Visit 5 3 years
Visit to outpatient clinic	*✔*	**–**	*✔*	*✔*	*✔*
History and current status	*✔*	**–**	*✔*	*✔*	*✔*
Physical examination	*✔*	**–**	*✔*	*✔*	*✔*
Electrocardiogram	*✔*	–	*✔*	*✔*	*✔*
Echocardiogram	*✔*	–	*✔*	*✔*	*✔*
Holter monitoring	*✔*	–	*✔*	*✔*	*✔*
Ergometry	*✔*	–	*✔*	*✔*	*✔*
Signal-averaged ECG	*✔*	–	–	–	*✔*
CMR	*✔*	–	–	–	*✔*
Blood analysis	*✔*	*✔*^a^	*✔*^a^	*✔*^a^	*✔*

Note: Subjects undergo several investigations as summarised in this table. They are requested to visit the outpatient clinic at baseline and at 1‑year intervals thereafter. Subjects randomised to eplerenone visit the outpatient clinic or their general practitioner after 1 week to check serum potassium and eGRF, which are also checked in these subjects at the yearly visits. Of note, all investigations except blood analysis are already performed as part of routine clinical care, which routinely includes evaluation of signs and symptoms of DCM and ACM. For the purpose of the study, we collect and use these available data.

*ECG* electrocardiography, *CMR* cardiac magnetic resonance, *eGFR* estimated glomerular filtration rate, *DCM* dilated cardiomyopathy, *ACM* arrhythmogenic cardiomyopathy

^a^ only for subjects randomised to eplerenone

### Study endpoints

The primary and secondary endpoints are listed in Tab. 3. The primary endpoint is a multiparametric assessment of disease progression defined as a responder-based composite primary endpoint (Tab. 3). If one of the predefined parameters of the composite primary endpoint is reached, CMR imaging is performed and study end date recorded. After a follow-up period of 3 years, outcomes will be assessed by an independent adjudication committee blinded to the allocated group. In case of a favourable trend (but no significant effect as yet), the DSMB may advise continuing the study for 2 more years (“adaptive design”).

**Table 3 Tab3:** Primary and secondary endpoints

*Primary endpoint*^a^
LV end-diastolic volume, increase > 10% (assessed with CMR)
LV ejection fraction, absolute decrease > 5% (assessed with CMR)
RV end-diastolic volume, increase > 10% (assessed with CMR)
RV ejection fraction, absolute decrease > 5% (assessed with CMR)
Late enhancement, absolute increase > 5% (assessed with CMR)
QRS voltage, decrease > 25% (ECG, measured in I, II and III in mV)
Occurrence of non-sustained ventricular tachycardia (Holter monitoring, exercise testing)
Heart failure signs and/or symptoms or arrhythmias necessitating medical treatment according to the guidelines and likely due to arrhythmogenic cardiomyopathy
*Secondary endpoints*
All individual components of the primary endpoint
Diagnosis of DCM (according to Mestroni criteria [19])
Diagnosis of ARVC (according to revised task force criteria [18])
Development of global or regional dysfunction and structural alterations (according to revised task force criterion 1 [18])
QRS axis (12-lead ECG)
Conduction intervals (PR interval, QRS duration [12-lead ECG; SA-ECG])
STT segment changes (12-lead ECG)
Change in biomarkers
Occurrence of sustained ventricular tachycardia or ventricular fibrillation
Hospitalisation for a cardiovascular reason

*LV* left ventricular, *CMR* cardiac magnetic resonance*, RV* right ventricular,* ECG* electrocardiogram,* DCM* dilated cardiomyopathy, *ARVC* arrhythmogenic right ventricular cardiomyopathy,* SA-ECG* signal-averaged electrocardiography

^a^The primary endpoint is a multiparametric assessment of disease progression defined as a responder-based composite primary endpoint. If one of the predefined parameters of the composite primary endpoint is reached, CMR imaging is performed and study end date recorded

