## Baseline results

In May 2014, the first participant was included into the study. Because of slow recruitment, in January 2018 it was decided to stop further inclusion of participants and complete the protocolled follow-up duration with the included cohort (*N* = 84). At this point, it had become clear that it was not realistic to assume that enough participants would be included to reach the originally defined composite primary endpoint (Tab. 3). Instead of a composite dichotomous endpoint, i.e. using the pre-specified cut-off values, individual components of the primary endpoint will now be analysed on a continuous scale to investigate possible significant differences. The statistical analysis plan was amended accordingly, and the decision to amend the study design, i.e. to stop inclusion of participants and to continue with the included cohort, was supported by the DSMB and the medical ethics committee. The primary objective remains showing that eplerenone retards disease progression. The majority of participants have now finished the study and the remaining participants are expected to finish in 2021.

An overview of the baseline characteristics of the 84 participants is provided in Tab. 4. By design, at baseline, all participants were in NHYA class I and had an LVEF > 45% and less than 2500 ventricular premature complexes (VPCs) during 24-hour Holter monitoring. Mean LVEF was 60% (±0.04). The median number of VPCs was 8 (0-1861). Baseline CMR scans were obtained for all 84 participants, but image quality was insufficient to perform adequate analyses in six cases. In the remaining 78 cases, as many as 14 cases (18%) showed LGE, mainly in the inferolateral left ventricular wall, suggestive of myocardial fibrosis. The six cases with insufficient image quality will be included for analysis of the other endpoints. An illustrative example is shown in Fig. 2. There were no statistically significant differences between the two groups in any of the baseline characteristics.

**Table 4 Tab4:** Baseline characteristics: no statistical differences between eplerenone and control group

	All	Eplerenone group	Control group
Number, *n*	84	42	42
Age at inclusion, years (SD)	39.5 (±13.1)	40.2 (±13.0)	38.8 (±13.4)
Male sex, *n* (%)	37 (44)	18 (43)	19 (45)
Body mass index, kg/m^2^ (SD)	25.7 (±4.8)	26.5 (±5.6)	24.9 (±3.6)
Systolic blood pressure, mm Hg (SD)	124 (±16)	128 (±17)	121 (±13)
Diastolic blood pressure, mm Hg (SD)	74 (±11)	75 (±10)	74 (±11)

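### The early-end rule written for the composite is not stated to have changed when its components became continuous outcomes, so early electrical or clinical progressors may contribute a CMR change over less than three years

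*Protocol article*

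**What the plan says.** - **Early-end rule.** The Study endpoints section, repeated in the footnote to Table 3, says: "If one of the predefined parameters of the composite primary endpoint is reached, CMR imaging is performed and study end date recorded". It is in the present tense.
- **CMR schedule.** Under Treatment: "CMR imaging and SA-ECG are performed at the start and end (36 months) of the study". Table 2 shows no CMR in between.
- **Interim assessments.** Also under Treatment: "electrocardiogram, Holter monitoring and ergometry are performed every 12 months".
- **Amended analysis.** Under Baseline results: "individual components of the primary endpoint will now be analysed on a continuous scale to investigate possible significant differences". The same section says that the analysis plan was amended to match.
- **Timing.** "In May 2014, the first participant was included into the study", and "in January 2018 it was decided to stop further inclusion of participants and complete the protocolled follow-up duration with the included cohort".
- **Missing data.** The Statistical analysis section gives one rule: the last observation is used. It also mentions repeated-measures or timing-based methods for changes over time, but only where suitable and without saying that actual scan dates enter the model.
- **Routine care.** The note to Table 2 says that "all investigations except blood analysis are already performed as part of routine clinical care".

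**The concern.** Ending a participant's study at the first event is coherent for the Kaplan-Meier and log-rank analysis of the composite, because nothing after the first event is needed. A continuous outcome needs every participant measured over the same interval, or the interval allowed for in the analysis. Under the rule as written, the interval depends on the outcome: someone with an ECG, arrhythmic or clinical event at year 1 or 2 is scanned then, and no later study scan is described.

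If eplerenone slows disease, such events are more common among controls. Control change is then truncated more often than eplerenone change, and an unadjusted comparison of baseline-to-last-scan change understates the benefit. The trial enrolled 84 of the 150 intended, so it has little power to spare. Enrolment began in May 2014 and the amendment came in January 2018, so some participants may already have ended early under the rule.

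**Working it through.** **1. The planning figure.** The Sample size estimation section assumes 50% of controls and, after a 50% relative reduction, 25% on eplerenone reaching the endpoint in 3 years. A two-sided Fisher exact test at 0.05 with 64 per arm has 80.2% power, so 128 reproduces. Inflation gives 128/0.90 = 143 and 128/0.85 = 151, so 150 fits the stated 10–15% loss. These rates are therefore usable as inputs.

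**2. Who can stop early.** Table 3 has eight components. Five are CMR measures, seen only at 36 months or on a scan triggered by something else. Only QRS voltage, non-sustained VT and the clinical component can trigger first.

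**3. Upper bound on early stopping.** Treat every event as detectable early, assume a constant hazard, and assign events to the next yearly visit. The share stopped by year t is 1 − (1 − p)^(t/3), where p is the 3-year rate.

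- Control, p = 0.50: year 1, 1 − 0.5^(1/3) = 20.6%; year 2, 1 − 0.5^(2/3) = 37.0%, or 15.5 of 42.
- Eplerenone, p = 0.25: year 1, 9.1%; year 2, 17.5%, or 7.3 of 42.
- Mean observed time, control: 0.206×1 + (0.370 − 0.206)×2 + 0.630×3 = 2.42 years. Eplerenone, in the same way: 2.73 years.

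Because CMR components cannot trigger early, real shares are lower. If half of events are detectable early (p = 0.25 and 0.125), the year-2 shares are 17.5% and 8.5%, with means of 2.73 and 2.87 years. If a quarter are (p = 0.125 and 0.0625), they are 8.5% and 4.2%, with means of 2.87 and 2.94 years.

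**4. Effect on the difference.** The article gives no progression rates or SDs, so these are assumed: mean change of 1.33 (control) and 0.67 (eplerenone) units per year, between-person slope SD 1, measurement SD 2, and correlation between slope and early trigger from 0 to 0.8. The true 3-year difference is 3 × (1.33 − 0.67) = 1.98, with SD √(9×1 + 4) = 3.61.

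With zero correlation the observed difference follows directly. At the upper bound it is 1.33×2.42 − 0.67×2.73 ≈ 1.39, and 1.39/1.98 = 70%. Simulation over all the correlations gives:

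| Events detectable early | True difference retained | Power, 42 per arm |
|---|---|---|
| None (all measured at 3 years) | 100% | 71% |
| A quarter | 89–94% | 65–67% |
| Half | 79–87% | 59–60% |
| All (upper bound) | 61–70% | 44–46% |

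Only 78 of the 84 baseline scans were analysable, an average of 39 per arm, so absolute power for CMR outcomes is somewhat lower throughout.

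**5. No treatment effect.** If eplerenone affects no component, both arms stop alike and the expected difference stays zero. This mechanism does not inflate type I error.

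**The case against.** The strongest reply is that the amended analysis plan is not shown. The early-end rule belongs to a composite that was replaced, the cohort was to complete its protocolled follow-up, and handling of unequal scan intervals is something an article normally leaves to the plan. The repeated-measures sentence points in that direction. It is also arguable that a final scan taken early is not a missing value, so the last-observation rule may not apply to it. This stands as a limit on certainty: the article does not establish that the rule survived. But the article still states the rule as current, the protocolled follow-up includes it, and no method for unequal intervals is given.

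A second reply concerns the remedy. The clinical component means a need for medical treatment, and eplerenone is described as maintained until the end of the study. Later values may therefore reflect treatment started or stopped after the event, while a scan at the event avoids that. This stands, and the fix allows for it.

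Four stronger readings are tempting but unsupported:

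- That all of the fastest progressors are cut short. Carriers who progress only on CMR stay to 36 months.
- That later diagnoses, arrhythmias and hospitalisations are lost. The text records a study end date; it does not say that these cease to be collected.
- That half or more of the true difference disappears. Even the upper bound from the article's own rates keeps 61–70% under the slopes assumed here.
- That the log-rank test is the problem. Scan-dependent event times would affect the composite, which has been replaced.

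**Conclusion.** The concern holds in limited form. Read as written, the early-end rule makes the CMR measurement interval depend on outcome, and the amended continuous analysis is not stated to allow for it. The direction, towards no effect if eplerenone works, follows from more controls being stopped.

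The size rests on assumptions. The ceiling of 37% of controls and 17.5% on eplerenone stopped by year 2 needs the planning rates, a constant hazard and every event detectable early. The retained shares, 61–70% at that ceiling and 79–94% if a quarter to a half of events are detectable early, also need the assumed slopes and SDs. The consequence is attenuation and lost power, not a false-positive risk. It should be corrected or clarified before analysis.

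**What to change.** 1. Analyse each continuous component by actual time from baseline to measurement. Use a mixed model with continuous time and a treatment-by-time slope, or annualised change.
2. State that an early value is not carried forward as the 36-month value.
3. For participants still in follow-up, record the event date and keep collecting routine-care data to 36 months. This concerns data collection only, not treatment.
4. For participants who ended early, retrieve routine 36-month data where they exist.
5. Report the analysis with and without post-event values, since these may reflect treatment changes after the event.

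The cost is a wording change in the protocol and analysis plan, plus retrieval of routine records. Since most participants had finished when the article was written, steps 1, 2 and 4 matter most. The slope approach assumes roughly linear change, and annualised change is noisier over short intervals. If the amended plan already models actual scan time, saying so would settle the analysis point.

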### Statistical analysis

After completion of the study, all eligible carriers who have been randomised to the treatment arm and received at least 1 dose of eplerenone will be used in the analyses of the primary and secondary efficacy endpoints, as well as in the safety analysis. Safety will be assessed by summarising the incidence and type of adverse events and the changes in laboratory parameters. The proportion of carriers experiencing serious adverse events and the proportion of carriers with noteworthy changes in laboratory parameters will be compared between treatment groups. The analysis of primary endpoints and secondary endpoints will be performed according to their assigned treatment group in accordance with the intention-to-treat principle. Additional analysis sets may be used in exploratory analyses. The number of subjects withdrawing from the study will be tabulated by their reasons for withdrawal and by treatment group. Potenzial biases due to withdrawal of subjects will be investigated. Baseline characteristics will be compared using chi-squared test (or Fisher’s exact test if appropriate). If differences are found, caution will be exercised when interpreting the results of the analyses between groups and methods may be modified to adjust for this difference.

The primary outcome will be presented by Kaplan-Meier curves for the treatment group, followed by the stratified log-rank test using stratification variables. Multivariate analysis will also be used to compare the endpoints between the two groups, adjusting for other variables including sex, age and screening centre. For missing data, the last observations made will be used. Unless stated otherwise, all secondary analyses will be performed using the same subjects included in the primary analysis. Secondary variables will be analysed using an appropriate statistical test, depending on the nature of the variable. Changes in parameters over time in the different treatment groups will be analysed using repeated measurement analysis or techniques that evaluate the timing of endpoints, when appropriate. For all tests, a *p*-value < 0.05 is considered statistically significant. Statistical analysis will be performed in SPSS (IBM SPSS Inc., Chicago, IL, USA; newest version at moment of analysis).

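### The rule that takes a CMR and ends the study when a component is reached is not reconciled with the month-36 CMR or the amended continuous analysis, so CMR changes may cover unequal, outcome-dependent intervals

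*Protocol article*

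**What the plan says.** Five statements in the protocol article bear on when the last CMR is taken and how it is used.

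- **Study endpoints, repeated in the Table 3 footnote:** "If one of the predefined parameters of the composite primary endpoint is reached, CMR imaging is performed and study end date recorded".
- **Treatment, and Table 2:** "CMR imaging and SA-ECG are performed at the start and end (36 months) of the study". No CMR is scheduled at year 1 or year 2. By contrast, "electrocardiogram, Holter monitoring and ergometry are performed every 12 months".
- **Baseline results:** inclusion stopped at 84 carriers, and in place of the dichotomous composite "individual components of the primary endpoint will now be analysed on a continuous scale to investigate possible significant differences". The trial would "complete the protocolled follow-up duration with the included cohort". On the analysis plan: "The statistical analysis plan was amended accordingly". That plan is not shown.
- **Statistical analysis, missing data:** "For missing data, the last observations made will be used".
- **Statistical analysis, change over time:** repeated-measurement or timing-based methods are allowed where appropriate.

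Five of the eight components in Table 3 are CMR measures: two volumes, two ejection fractions and late enhancement. The other three are QRS voltage, non-sustained ventricular tachycardia, and heart failure or arrhythmia needing treatment.

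**The concern.** A CMR at the first component reached suits a time-to-first-event composite, where reaching a component is the outcome and follow-up can stop. It does not suit a continuous comparison of CMR change, because the length of the measurement interval then depends on how the carrier fared.

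Between the two scheduled scans, only the three non-CMR components can be detected on schedule. An early trigger would therefore usually come at about month 12 or 24, or whenever a clinical event occurs. If that scan is the carrier's last, 12 or 24 months of change is set beside 36 months in everyone else. If early events mark faster progression, the shortest intervals fall on the fastest progressors. If eplerenone works, they fall more often on controls.

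The CMR measures are most of the components now to be analysed continuously. The cohort is 84 against the 128 the sample size section calls for, with 78 analysable baseline scans. Any avoidable distortion of the CMR contrast is costly.

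**Working it through.** **1. The plan's own figure.** For 50% against 25% at two-sided 0.05 (sidedness is not stated), 64 per group gives 80.2% power with Fisher's exact test, so the stated 128 is reproduced. The point below does not depend on it.

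**2. The sections side by side.** Treatment and Table 2 fix the last CMR at month 36, with no exception. Study endpoints attaches a CMR and the study end date to the first component reached. Treatment ties the final CMR to the end of the study, so the natural reading is that the triggered scan is the last one. Baseline results neither withdraws the trigger nor says that a month-36 scan follows it. The last-observation rule, if applied to CMR, would put the early scan in the 36-month slot.

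**3. Size, under assumptions.** The article gives no progression rate and no early-event rate, so these inputs are assumed:

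- control mean 3-year change *m* = 1 unit; eplerenone halves it, so the true difference is 0.5;
- linear progression;
- a share *p* of each arm has an early event and is scanned at a mean of 1.5 years (months 12 and 24 equally likely);
- those carriers progress *r* times as fast as the others, with *r* from 1 to 3;
- eplerenone halves *p*, by analogy with the halving assumed for the whole composite.

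The observed mean change in an arm is *m* × (1 − *p* + *pr*/2) / (1 − *p* + *pr*).

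Example with *p* = 0.20 in control, 0.10 on eplerenone, *r* = 2:
- control: 1 × 1.0/1.2 = 0.833
- eplerenone: 0.5 × 1.0/1.1 = 0.455
- difference: 0.379, and 1 − 0.379/0.5 = 24% attenuation

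| Early share, control / eplerenone | *r* = 1 | *r* = 2 | *r* = 3 |
|---|---|---|---|
| 10% / 5% | 0.463 (7%) | 0.433 (13%) | 0.409 (18%) |
| 20% / 10% | 0.425 (15%) | 0.379 (24%) | 0.348 (30%) |
| 33% / 17% | 0.375 (25%) | 0.322 (36%) | 0.294 (41%) |

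A simulation in which individual slopes drive a yearly event hazard gave 14% to 43% attenuation when 18% to 43% of controls had an early event.

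**4. Direction under other assumptions** (control minus eplerenone change):

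- Slower CMR progression but equal early shares of 10% to 33%: 0.475 to 0.350 against 0.5, still attenuated.
- No effect on CMR progression, early events halved (20% / 10% or 33% / 17%): −0.05 to −0.11 against 0, a shift to apparent harm.
- No effect on either: no bias.
- More early events on eplerenone (10% control, 20% eplerenone, *r* = 2): 0.492 against 0.5, almost unchanged.

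**5. Power.** With 78/2 = 39 per arm (an even split is assumed) and an assumed true standardised difference of 0.65, power is 82%. With 20% attenuation it is 63%, and with 40% it is 41%.

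**6. Does using scan dates help?** A second simulation assumed LVEDV rising 2% per year in control and 1% on eplerenone, between-carrier SD 2% per year, noise SD 4% per scan, and 36 pairs per arm. The true 36-month difference is 3 × (2 − 1) = 3.0 points.

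- With 10%, 20% and 30% of controls triggering early (6%, 13%, 20% on eplerenone), raw last-minus-baseline change gave 2.69, 2.41 and 2.16. Power fell from 34% to 30%, 26% and 23%.
- Change per year × 3 returned 3.0 each time. Its SD rose from √(9 × 2² + 2 × 4²) = 8.2 to 9.0, 9.7 and 10.5, and its power was no better than that of the raw analysis.

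**The case against.** The strongest reply has four parts.

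- **The month-36 scan is never cancelled.** Table 2 schedules it for everyone, and Baseline results speaks of completing the protocolled follow-up. The trigger is worded for the composite, which that section treats as the original design, so it may have lapsed. This stands as a possible reading. But the trigger remains in the text and the footnote, and the Discussion still describes the composite as adopted. The reader cannot tell which applies.
- **No section prescribes raw last-minus-baseline change.** The amended analysis plan is unseen, and the article allows timing-based methods. This also stands: the plan may already handle scan dates. The one visible rule that points the other way is last observation used. No analysis plan can supply a month-36 scan that was not taken.
- **Early triggers may be few.** Carriers entered without non-sustained ventricular tachycardia, in NYHA class I and with a median of 8 ventricular premature complexes. The 50% control rate covers all eight components, five of them not scheduled for measurement before month 36. The 33% scenario is therefore high; at 10% the attenuation is 7% to 18%.
- **Linear progression is assumed.** An abrupt CMR change at the event would reduce the bias.

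A reader might infer that the CMR results are necessarily biased towards no effect. The documents do not support that: step 4 of the working shows that the direction depends on what eplerenone does to CMR progression and to early events.

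**Conclusion.** The sections on CMR timing do not agree, and the change to continuous components left the disagreement unresolved. On the natural reading, together with an analysis that ignores scan date, CMR changes are compared over unequal intervals that depend on outcome.

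Under the trial's own hypothesis and roughly linear progression, the arm difference is attenuated by about 7% to 41% for early-event shares of 10% to 33% in control. If eplerenone reduces early events without slowing CMR progression, the contrast moves to apparent harm by 5% to 11% of the control 3-year change. If it affects neither, there is no bias. Early-event shares, slope ratio, early scan time and standardised effect are all assumptions, so these figures show what is possible and do not estimate what happened.

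It would go too far to say that the month-36 CMR is replaced as a matter of record, or that the planned analysis is known to be wrong.

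**What to change.** 1. Reconcile Treatment with Table 2, Study endpoints with the Table 3 footnote, and Baseline results. State whether a carrier who reached a component early also has the month-36 CMR.
2. For carriers still in follow-up, keep the scheduled month-36 CMR after a triggered one, and use the triggered scan as an additional time point.
3. For all carriers, analyse CMR change by actual scan date: change per year between the two scans, or a mixed or joint model with continuous time, with the contrast expressed at 36 months. A joint model with the trigger addresses the link between scan time and progression directly.
4. Do not carry an early CMR forward as the 36-month value.
5. Report scan intervals by arm.

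The cost is a few sentences in the analysis plan and the use of scan dates, plus one already scheduled scan for a small number of carriers. There are real downsides:

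- Slopes over short intervals are noisier, and annualising assumes near-linear progression.
- A month-36 scan after a clinical trigger may reflect treatment started since.
- Most carriers had finished when the article was written, so step 2 reaches few. For those already ended early, step 3 addresses the bias but does not recover the lost power.
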